**Fig 3 pone.0358356.g003:**
[figure not shown]
Phased framework for development and implementation of a community-based integrated healthcare model by assessing the feasibility and acceptability for improving functional ability and quality of life among the tribal population in East Singhbhum.

The development of the healthcare model will follow a systematic approach beginning with an in-depth analysis of phase 1 findings. It will be conducted in the following three steps.

#### Step 1: Identification and Confirmation of Healthcare Model Domains.

Phase 1 findings (both quantitative and qualitative) will be integrated and analysed to identify priority key health needs, functional decline patterns, healthcare service gaps, and socio-cultural determinants. Evidence from the literature and existing healthy ageing frameworks will further support the identification and confirmation of the core healthcare model domains.

#### Step 2: Stakeholder Consultation and Healthcare Model Development.

A draft model will be developed using evidence-based, culturally appropriate strategies. It will be refined through stakeholder consultations (tribal leaders, ASHAs, NGOs, public health experts, Pradhan etc.) to ensure feasibility and acceptability, leading to finalisation of domains and model. A gender-stratified approach will guide tailored interventions. The healthcare model will adopt a gender-stratified approach, using questionnaire findings to identify gender-specific health needs, risks, and barriers and design tailored interventions. For men, this will focus on non-communicable diseases, substance abuse, and occupational risks, while for women, it will address reproductive health, nutrition, chronic conditions, and caregiver burden. Service delivery will also be adapted, with community or workplace outreach for men and mobile camps, home visits, and empowerment initiatives for women, ensuring a holistic response to biological, social, and cultural determinants of health.

**Step 3: Implementation.**

### Assessment of the effectiveness of the model

The finalised model will then be implemented in a selected village, incorporating components such as health checkup, nutrition support, physical and mental health interventions, and home-based care. Further the effectiveness of the model will be evaluated using pre-post measures of functional ability and quality of life.

### Feedback and refinement

Qualitative feedback from participants and key stakeholders will assess feasibility & acceptability. Their perspectives will be systematically elicited, analysed, and incorporated into the model’s refinement.

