**Component E: A: Access through Community & Digital Connectivity**

Each month, the Sahiyas and CHOs organise a village-level event called “Elderly Day” to offer regular health examinations, health education, and chances for social interaction and community involvement.

CHOs will facilitate teleconsultations, connecting older adults with off-site specialists, including geriatricians, dietitians, and AYUSH practitioners, for remote assessment and management.

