### Data collection procedure

The data collection for the mixed-method study will begin by obtaining necessary approvals from the Institutional Ethics Committee (IEC), Institutional Scientific Committee (ISC), and administrative permissions from the State Tribal Welfare Department, District Health Authorities, and Panchayat-level leaders in the selected districts. Community sensitization meetings will be held in each selected village to inform local leaders, ASHA workers, and residents about the study’s purpose and procedures, thereby building trust and encouraging participation. A household listing will be conducted to identify eligible individuals aged 45 years and above, including both middle-aged (45–59 years) and elderly (60 + years) participants. Informed consent will be obtained, and for illiterate participants, thumb impressions will be taken in the presence of a witness to ensure ethical participation.

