#### Sources of bias and mitigation strategies.

The study identifies potential sources of bias related to participant selection, communication, measurement, and data management. Measures will be taken to reduce these biases and improve the validity of the findings.

Selection Bias

Source: Selection bias may arise if the study participants do not adequately represent the diversity of tribal populations in the study area.Mitigation: A multistage stratified random sampling approach will be used to enhance representativeness across tribal populations, including Scheduled Tribes (STs) and Particularly Vulnerable Tribal Groups (PVTGs). Villages will be selected across five blocks to ensure adequate geographical coverage.

2. Duplication and Participation Bias

Source: Bias may occur among individuals already participating in similar health interventions or research studies.Mitigation: Individuals currently enrolled in similar health-related interventions or research studies will be excluded to minimize duplication and potential influence on study outcomes.

3. Information and Communication Bias

Source: Differences in literacy, language, and cultural context may affect participants’ understanding of study information and interview questions.Mitigation: Village-level sensitization meetings will be conducted with community leaders, Sahiya/ASHA workers, and residents. Information will be provided in an understandable and culturally appropriate manner. For illiterate participants, consent will be documented through a thumb impression in the presence of a witness. Support from Sahiya/ASHA workers will also be sought to facilitate communication and community engagement.

4. Recall and Measurement Bias

Source: Participant recall and reliance on self-reported information may result in inaccurate reporting of health conditions or functional status.Mitigation: The concurrent mixed-methods approach will enable triangulation of findings across quantitative and qualitative data. Standardized and validated instruments, including the Barthel Index, Lawton IADL Scale, and WHOQOL-BREF, will be used to improve the consistency of measurement.

5. Data Management and Researcher Bias

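### Phase 2 acceptability and self-reported pre-post outcomes are at risk of favourable bias: no stated route to residents who do not engage, and people who shape or deliver the model may also appraise it or assist at interview

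*Protocol article*

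**What the plan says.** **Who judges acceptability.** Feedback and refinement states: "Qualitative feedback from participants and key stakeholders will assess feasibility & acceptability". The next sentence gives the use: "Their perspectives will be systematically elicited, analysed, and incorporated into the model’s refinement". Table 4, row 4 (Phase 2 evaluation) repeats the qualitative feedback and adds tracking of utilisation and of participation in health screening.

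**Who shapes the model.** Step 2 says of the draft model: "It will be refined through stakeholder consultations (tribal leaders, ASHAs, NGOs, public health experts, Pradhan etc.) to ensure feasibility and acceptability". The Phase 2 section of Study procedure adds traditional healers and Medical Officers to those consulted.

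**Who delivers it.** The same Phase 2 section seeks ASHA/Sahiya support for mobilising participants and for implementation. Table 3 gives ASHAs screening and home visits. Component A has Medical Officers supporting the mobile clinics in rotation. Component E says: "Each month, the Sahiyas and CHOs organise a village-level event called “Elderly Day".

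**How effectiveness is judged.** After implementation in a single village: "Further the effectiveness of the model will be evaluated using pre-post measures of functional ability and quality of life". Table 4, row 3 specifies the Phase 1 tools, and no comparator is named. Short-term change in self-rated health and quality of life is listed under Primary outcome.

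**Who helps at interview.** Item 3 of Sources of bias and mitigation strategies names poor understanding of study information and interview questions as a source of bias. Among the remedies is: "Support from Sahiya/ASHA workers will also be sought to facilitate communication and community engagement". No phase is named. The Phase 1 part of Study procedure says that trained investigators administer the questionnaire. Nothing equivalent is said for Phase 2.

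**The concern.** Objective 3 is about feasibility and acceptability. An acceptability finding is most useful when it includes those who did not take the service up, because they can say what was unacceptable or out of reach. It is weakest when it comes from users and from people with a stake in the model.

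The second issue is courtesy reporting. A person asked about function, quality of life or satisfaction may answer more kindly when the worker who provided the service is helping with the interview. In a one-village pre-post design with no comparator, that shift falls directly on the estimated change.

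At stake are the reading of the pilot as evidence of acceptability or short-term benefit, and the refinement of the model, which needs to know why people stay away. The Abstract expects a validated and scalable model to come out of this work.

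**Working it through.** The document gives no figure for this point. The only sample-size calculation (520 participants) is for the Phase 1 survey, and the argument does not use it. The check is therefore mainly a comparison of sections.

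**1. Is there a route to non-users?** Feedback and refinement and Table 4, row 4 name participants and key stakeholders. Neither mentions residents who use the model little or not at all. Utilisation tracking would identify them in number. The Gender Bias item itself expects that some men may engage less with health services. The means to reach non-users partly exists, since Data collection procedure says: "A household listing will be conducted to identify eligible individuals aged 45 years and above". That listing is described for the survey villages, and the protocol does not say whether the pilot village is one of the 25.

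**2. Do the roles overlap?**

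| Role group | Consulted on the model | Helps deliver it | Could be a feedback stakeholder |
|---|---|---|---|
| ASHAs/Sahiyas | Yes (Step 2) | Yes (Phase 2 section, Table 3, Component E) | Not excluded |
| Medical Officers | Yes (Phase 2 section) | Yes (Component A) | Not excluded |
| Tribal/local leaders | Yes (Phase 2 section, Step 2) | Support sought from community stakeholders | Not excluded |

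Step 2 asks these groups to make the model feasible and acceptable, and the feedback stage may ask the same groups whether it is. The overlap shown is of roles.

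**3. Can a delivering worker assist at the post-implementation interview?** Item 3 of the bias section permits it, because its remedy covers interview questions and is not tied to a phase. The statement on trained investigators is made for Phase 1 only. The same Sahiya help could occur at baseline. The difference is that at baseline she had not yet delivered the service.

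**4. Is the risk addressed elsewhere?** The six listed bias sources do not include favourable reporting after delivery, or appraisal by co-designers. Self-report is treated as inaccuracy, with triangulation and validated instruments as the remedies.

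**5. Scale, on assumed inputs only.** Suppose there is no true change, and reporting shifts by d standard deviations of the change score among N respondents. A two-sided 5% test of the mean change then favours the model with probability Φ(d√N − 1.96). Neither d nor N is in the protocol. N = 21 is roughly one village's average share of the survey (520/25 = 20.8); 50 and 100 are arbitrary.

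| N | d = 0 | d = 0.1 | d = 0.2 | d = 0.3 |
|---|---|---|---|---|
| 21 | 2.5% | 6.7% | 14.8% | 27.9% |
| 50 | 2.5% | 10.5% | 29.3% | 56.4% |
| 100 | 2.5% | 16.9% | 51.6% | 85.1% |

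For example, with N = 50 and d = 0.2: 0.2 × √50 = 1.414, and Φ(1.414 − 1.96) = 29.3%. The table shows that a modest reporting shift could matter. It does not show that one will occur.

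**The case against.** The strongest reply is that much of the worry lies in what the text permits and not in what it prescribes. Five stronger readings are tempting, and the documents do not support them.

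- *Acceptability rests on feedback alone, and non-attenders are excluded.* Table 4, row 4 also tracks utilisation and screening participation. The protocol does not define participants as attenders, and someone who consented and then came rarely could be included. What stands is that no route to non-users is stated and that counts do not give reasons.
- *Those who designed the model will grade it.* The text does not say that the feedback stakeholders are the individuals consulted in Step 2. Stakeholder acceptance is also part of the stated secondary outcome, and using feedback to refine a pilot is ordinary practice. The overlap of roles stands, and with it the need to keep the two kinds of feedback apart.
- *Sahiyas will sit in on Phase 2 interviews.* This is a permitted reading, not a stated procedure, and the same help could be present at baseline.
- *Acceptability will be overstated by a given number of points.* Assume 90% approval among users, 30–50% among non-users and 40–80% uptake. The gap then runs from 90 − (0.8 × 90 + 0.2 × 50) = 8 points to 90 − (0.4 × 90 + 0.6 × 30) = 36 points. Every input is invented, and the plan reports no such percentage, because its acceptability assessment is qualitative.
- *Barriers will go unheard.* Phase 1 interviews already explore access and the acceptance of community-based care. They precede the model, however, so they cannot explain why people did not use it.

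It is also fair to say that an article may leave the choice of feedback interviewees and interviewers to the full protocol. The point rests on what the article does fix: the named sources and an interview remedy with no phase limit.

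**Conclusion.** The point holds as a risk of favourable bias in Phase 2 acceptability and in the self-reported pre-post outcomes. It is not a demonstrated bias. It rests on three features of the text: named feedback sources with no stated route to those who do not engage, role groups that appear in design and delivery and may appear in appraisal, and Sahiya/ASHA interview support that is not limited to Phase 1. The single-village pre-post design with no named comparator gives such bias nothing to be checked against.

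The size cannot be derived from the documents. Feedback used to improve the model is legitimate. The problem arises when it, or the pre-post change, is read as evidence that the model is acceptable or effective. This is an inexpensive improvement that should be made before implementation, planned for June to August 2027.

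**What to change.** 1. **Feedback and refinement; Table 4, row 4.** State that eligible residents of the pilot village will be listed, and that the feedback interviews will include some with no or low recorded use, identified from the utilisation tracking already planned.
2. **Same places.** Report feedback from people who designed or delivered the model as provider feasibility, separately from resident acceptability.
3. **Sources of bias, item 3.** State that workers delivering the model in the pilot village neither facilitate nor attend the Phase 2 pre-post and feedback interviews, and that the trained investigators described for Phase 1 conduct them.

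**Cost.** Mainly protocol wording, with some feedback interviews directed to non-users. Non-users are harder to reach. A household listing is needed if the pilot village is not one of the 25 survey villages. Investigators will have to manage language needs without the local Sahiya.

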### Detailed intervention outline

#### HOR-SATHI Healthy Ageing Model.

**Component A: H: Health Outreach & Clinical Care**

Monthly Mobile Healthcare Clinics to be staffed by Community Health Officers (CHOs) or ANMs, with rotating support from Medical Officers.Regular WHO ICOPE-based geriatric-NCD screening for cognitive, locomotor, nutritional, psychological, visual and auditory impairments, along with blood pressure, blood glucose, and functional status assessment, followed by risk-based referral and care.Integration of AYUSH services by having an AYUSH doctor or qualified practitioner on hand in mobile clinics to offer supportive management for chronic diseases based on Ayurveda or yoga in addition to traditional allopathic treatment.

**Component B: O: Optimal Nutrition & Well-being**

Training Sahiyas and Anganwadi workers in nutritional assessment, including the use of the Mini Nutritional Assessment, and providing appropriate dietary counselling.Promoting dietary diversity and kitchen gardens to increase the consumption of locally available, iron- and calcium-rich tribal foods.

**Component C: R: Rehabilitative & Functional Support**

Elderly Support Groups: Establishment of gender-stratified peer support groups to reduce social isolation and strengthen existing community networks through Self-Help Groups (SHGs)

Multidimensional RehabilitationMental: Counselling provided by trained personnel from the District Mental Health Programme.Physical: Home-based rehabilitation exercises taught to family caregivers by trained volunteers, yoga instructors, or physiotherapists.Social: Promoting mutual support, trust and collective participation within the tribal community through “Gram Chaupal” for better health.

**Component D: S: Social Protection & Entitlement Linkage**

Facilitate enrolment in Ayushman Bharat, Arogya Mandir services, and relevant social security and pension schemes.Aadhaar Facilitation by coordinating with local Panchayat members, elderly tribal leaders to address documentation gaps and other practical barriers to scheme enrolment.

**Component E: A: Access through Community & Digital Connectivity**

Each month, the Sahiyas and CHOs organise a village-level event called “Elderly Day” to offer regular health examinations, health education, and chances for social interaction and community involvement.

CHOs will facilitate teleconsultations, connecting older adults with off-site specialists, including geriatricians, dietitians, and AYUSH practitioners, for remote assessment and management.

**Component F: T: Traditional Medicine Validation**

Systematic documentation of local tribal healing practices and their role in community healthcare.Local healing practices will be assessed by experts in AYUSH (Ayurveda, Yoga, Naturopathy, Unani, Siddha & Homeopathy) with safe and appropriate practices incorporated into the care pathway, while potentially harmful practices will be addressed through culturally sensitive, non-confrontational community education.

**Component G: H: Human Resource Capacity Building (Training-of-Trainers Model)**

Training of trainers- Master trainers (geriatric/public health faculty) will train CHOs/ANMs, who will subsequently train Sahiyas and selected grassroots-level healthcare workers and community volunteers, preferably male, to facilitate culturally appropriate engagement while maintaining gender balance and avoiding gender bias in community participation and service delivery.Empowering Hamlets: Training volunteers from within the tribal community to extend healthcare services to remote areas with limited access to regular frontline health workers.

**Component H: I: I**ntegrated Care Coordination: Coordinating referrals, follow-up, and continuity of care across community, primary, secondary, and tertiary healthcare services.

**Operational Framework Table for Proposed Healthcare intervention**

#### Rationale behind the development of a community-based, culturally sensitive healthcare model.

The proposed healthcare model incorporates several innovative features that distinguish it from existing community-based and healthy ageing models in tribal settings. These features are intended to enhance cultural relevance, programme integration, and responsiveness to the healthcare needs of middle-aged and elderly tribal populations.

Age group inclusion-Includes participants belonging to both the middle-aged and elderly categoriesGender- and Age-Sensitive – Interventions are differentiated for men and women and specifically adapted for the elderly.Integration of Modern & Traditional Systems- Acknowledges traditional healing instead of sidelining it, to improve community trust.Nutrition-Care Linkage – Direct incorporation of local dietary practices and nutrition-sensitive interventions.Community Empowerment – Uses existing social capital (Self Help Groups (SHGs), village councils) to drive awareness and decision-making.Programmatic Convergence → Brings together NPHCE, NPCDCS, NHM, and nutrition schemes under one framework in tribal areas.

Monitoring Beyond Disease Outcomes → Tracks functional decline, quality of life, autonomy, and cultural acceptability — indicators usually ignored in mainstream programs.

#### Adaptability, scale-up, and sustainability of the model.

The proposed healthcare model is designed to support replication, scale-up, and long-term sustainability by integrating community-based care with existing health systems and national programmes.

Application in Other Settings (Replicability)

Phased Development Framework: The model follows a three-step process of domain identification, model finalization, and implementation, allowing local health needs and socio-cultural factors to be assessed before intervention delivery.Early Intervention: Inclusion of individuals aged 45 years and above enables early identification and management of functional decline, particularly in resource-constrained and socially disadvantaged populations.Contextual Adaptation: The model begins with an assessment of local strengths and challenges, allowing interventions to be adapted to the infrastructure, resources, and needs of different communities.Cultural Adaptation: Culturally relevant strategies, including local dietary practices and indigenous knowledge, can be modified according to the cultural context of other populations.

Scaling Up the Model

Programmatic Convergence: The model integrates existing programmes, including NPHCE, NPCDCS, NHM, and nutrition programmes such as Poshan Abhiyan, through coordinated referral and monitoring pathways.Institutional Adoption: Findings may support the adoption of the model by district- or state-level health authorities and its integration into existing health programmes.Expansion to Other Settings: Evidence generated through the pilot implementation may inform adaptation and scale-up in other tribal districts and settings with similar healthcare disparities.Policy Integration: The findings may provide evidence to inform future policies and programmes in geriatric and tribal health.

Long-Term Sustainability

Community Ownership: Engagement of tribal leaders, Panchayats, NGOs, and other community stakeholders can promote local ownership and sustained participation.Local Capacity Building: Strengthening the capacity of Sahiyas/ASHAs and tribal volunteers can support continued community-level screening, health promotion, and home-based follow-up.Reduction of Economic Burden: Preventive and community-based care may help reduce avoidable healthcare expenditure and the financial burden associated with chronic disease and functional disability.Integration of Traditional Practices: Appropriate engagement with traditional healers may strengthen community trust and support culturally acceptable healthcare delivery.Use of Existing Social Structures: Engagement of Self-Help Groups (SHGs), village councils, and other established community networks can support continued health awareness, participation, and decision-making.

